### Monitoring the impact of population drift and adaptive randomization

There could be a drift in our population characteristics that are related to outcome [46]. This is a problem for all trials, whether they are equally or adaptively randomized. A recent paper examined the effects of response probabilities that changed over time due to this population drift, and found that population drift had little effect on adaptive randomization [47]. However, given our large dataset, we may be in a unique position to contribute to understanding how adaptive randomization might interact with population drift. In order to determine whether drift occurs, we will monitor the characteristics of the study population over time—especially focusing on drift introduced (or magnified) by adaptive changes in our random allocation rule. We will focus on several factors that are known to be associated with abstinence from smoking. These factors include cigarettes per day, time to first cigarette, sex, age, and income [48]. If we find that sample characteristics become unbalanced, we will adjust our outcome analyses to account for this. In addition, in secondary outcome analyses, we will track 1-month abstinence to determine whether rates changed over time. If we find significant changes in either population characteristics or abstinence over time, we will investigate whether (1) population drift, (2) temporal changes in the randomization scheme, or (3) a combination of the two had an effect on the proportion of patients who quit smoking.

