#### Month-1 call for service data collection and informed consent

In accordance with standard procedures in the existing UKanQuit treatment program [20, 24], study staff will call all patients at 1 month post enrollment to assess outcomes including smoking status, quit attempts, counseling utilization, medication use, and other factors related to quitting (see Table 3, Core study measures). At the close of the call, study staff will verbally debrief patients on their inclusion in the trial and invite them to participate in the study. Study staff will collect additional data related to study outcomes.

**Table 3 Tab3:** Core study measures

	Baseline	Month 1	Month 6
Outcomes			
7-day point-prevalence abstinence		✓	✓
Biochemical quit verification		✓	✓
Number of quit attempts since enrollment		✓	✓
Post-discharge counseling adherence/other support		✓	✓
Medication use/adherence		✓	✓
Sociodemographics/mediators/moderators			
Demographics: age, gender, race	✓		
Length of hospital stay (for index visit)	✓		
Reason for hospitalization (index visit)	✓		
Readiness to quit, craving/withdrawal	✓	✓	
Number of cigarettes per day (cpd); time to first cigarette	✓	✓	
Motivation/confidence quit/stay having quit	✓	✓	
Default constructs (perceived status quo, etc.)		✓	
Rehospitalization		✓	✓
Cost measures			
Counseling		✓	✓
Nicotine Replacement Therapy (NRT) (calculated from patient self-reported use)		✓	✓

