## Data analysis

### Overview of hypotheses and analyses

**Table 4 Tab4:** Virtual response patterns for quit rate endpoint

	OPT IN	OPT OUT	
		Efficacy	
No differences	15.7%	15.7%	Both have equal quit rates
Small but unlikely	15.7%	20.0%	OPT OUT is moderately better
Expected	15.7%	25.2%	OPT OUT is better at expected differences

The overall design is a randomized controlled trial (RCT) with individual assignment to groups. Bayesian analysis will drive participant allocation. Prior to outcome analyses we will examine baseline data to evaluate if randomization achieved equivalent groups. In addition, we will conduct process, outcome, mediation, and cost analyses.

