#### Bayesian design

We will perform a prospective randomized comparative effectiveness *Bayesian adaptive design study* [34]. Our endpoint is the percentage of patients with verified cessation at 1 month (4 weeks) post randomization. We will perform our first planned interim analyses when we have endpoint data on 400 patients. The arm that appears to be performing the best will get more participants allocated to it in the subsequent randomization period. A new adaptive randomization structure will be updated every 13 weeks, using up-to-date outcome data, until the trial meets success or all 1000 subjects are consented. The main outcome analysis will use an ITT approach, with the denominator being all participants randomized to the study. Data from patients we are unable to reach at 1 month will be de-identified and included in data analyses.

For this study the primary endpoint is modeled:
*S*
_*QjT*_|*n*
_*jT*_ ~ Bino(*n*
_*jT*_
*,θ*
^*Q*^
_*j*_) quitting.

In addition, we provide “weakly informative” priors:logit(*θ*
^*Q*^
_*j*_) ~ N(0,100^2^).

Using the endpoint data and the prior probabilities, we then use Markov Chain Monte Carlo computations to obtain the Bayesian posterior distributions for the endpoint (i.e., quitting). We will stop randomizing into the comparative trial if the probability of a study arm having maximum utility is greater than 0.9925. The arm having the maximum quit rate is *M*
_*T*_ = max(*θ*
^*Q*^
_*1,*_
*θ*
^*Q*^
_*2*_). The stopping rule is mathematically *P*(*M*
_*T*_ > .9925). If a maximum arm is not identified after 500 patients, this procedure and accrual will continue until a maximum arm is identified or we enroll all 1000 patients. It is possible that we will reach the maximum utility criterion before 1000 patients are consented. Should this occur, we will stop the trial and begin outcome, cost, and mediation analyses in order to quickly disseminate findings.

After the maximum arm probability is evaluated, the next round of patients is randomized using a formula that favors the arm with the maximum quit rate, thus taking advantage of the information gained from our interim analyses. Using this formula, each arm is allocated for the next patients to be enrolled in the *j*
^th^ arm proportional to:$$ {V^{\ast}}_j=\mathrm{sqrt}\Big(\Pr \left({M}_{jT}={\theta^Q}_1\Big)\mathrm{Var}\left({\theta^Q}_1\right)/\left({n}_{jT}+1\right)\right). $$

This type of allocation has more desirable properties than simply using Pr(*M*

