_*jT*_ = *θ*
^*Q*^
_*1*_). In other words, using this approach will allow us to assign more patients to the most promising arm, and fewer patients to the least. Regardless of when the maximum arm probability cut point is reached, we will confirm this finding with a subsequent analysis and evaluation (> .99) after all data from all enrolled patients are obtained, as some will be in the study when early success criteria are identified.

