Hypothesis 1: compared to OPT IN, significantly more patients in OPT OUT will participate in counseling, use cessation medications, and be abstinent from smoking	Abstinence: treatment condition and 1-month 7-day point-prevalence abstinence	2-sample binomial test
	Counseling: treatment condition and total counseling time by 1 month	2-sample lognormal test
	Medication: treatment condition and number of days of medication use	2-sample Poisson test
Hypothesis 2: significantly more smokers in OPT OUT will be abstinent from smoking, and mediation analyses will partially or fully explain the effects	Treatment condition and 6-month and • 7-day point-prevalence abstinence • Default variables • Counseling/medication use	Bayesian structural equation modeling with a logistic outcome
Hypothesis 3: OPT OUT will be more costly but also more effective than OPT IN	Treatment condition and 1-month abstinence • Variable costs	Incremental cost/quit

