#### Analyses by aim

The main analyses for each aim are outlined below (Table 5).

Aim 1. Hypothesis 1: among patients consented into the trial, significantly more patients in OPT OUT will participate in counseling, use cessation medications, and be abstinent from smoking at 1 month post randomization compared to OPT IN. These analyses will involve two-sample tests.

Aim 2. Hypothesis 2: significantly more smokers in OPT OUT will be abstinent from smoking, and mediation analyses will find that counseling participation, medication use, and default-theory-based variables will partially or fully explain the effect of OPT OUT on cessation at 6 months post randomization. After identifying a structural equation model that adequately fits the data for the hypothesized associations between the intervention and 6-month outcome, i.e., that Comparative Fit Index (CFI) > .9 and Root Mean Square Error of Approximation (RMSEA) < .8, we will examine mediation using approaches based on the work of MacKinnon et al. [49], Brown [50], and Shrout and Bolger [51]. Our theoretical model (Fig. 1, Significance) will guide our analysis.

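### Observed imbalance can switch the outcome analysis from unadjusted to adjusted, and the article does not say whether the adjusted result then decides the trial

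*Protocol article*

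**What the plan says.** The main comparison is written without covariates. The section Bayesian design models the number of quitters in each arm as binomial with a vague prior. It gives the early rule, "We will stop randomizing into the comparative trial if the probability of a study arm having maximum utility is greater than 0.9925", and the final one, "we will confirm this finding with a subsequent analysis and evaluation (> .99) after all data from all enrolled patients are obtained". Table 5 lists the abstinence comparison under Hypothesis 1 as a "2-sample binomial test", and Analyses by aim says of Aim 1: "These analyses will involve two-sample tests".

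Two other places bring in baseline data. Overview of hypotheses and analyses says: "Prior to outcome analyses we will examine baseline data to evaluate if randomization achieved equivalent groups". Monitoring the impact of population drift and adaptive randomization goes further: "If we find that sample characteristics become unbalanced, we will adjust our outcome analyses to account for this". That section also names predictors of abstinence: "These factors include cigarettes per day, time to first cigarette, sex, age, and income". Table 3 shows cigarettes per day and time to first cigarette at baseline, together with "Demographics: age, gender, race".

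**The concern.** The adjustment sentence is a stated rule, and it makes the form of the outcome analysis depend on the data. It is not confined to supportive work: the article has a separate section for sensitivity analyses, and the next sentences of the drift section turn to secondary outcome analyses as something additional. The natural reading is that the main analysis is included. The article does not say whether the adjusted result then replaces the unadjusted one at the >.99 confirmation.

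Imbalance is also the wrong criterion. The value of adjusting for a covariate depends mainly on how strongly it predicts quitting, and the article already names factors it regards as predictive. Under randomization, a check for imbalance mostly detects chance. At stake are a clear primary decision and a modest amount of precision.

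**Working it through.** **The plan's own figures.** Quit rates: 0.30 × 0.29 + 0.70 × 0.10 = 0.157 and 0.80 × 0.29 + 0.20 × 0.10 = 0.252, as stated. Success probabilities: 92% + 3% = 95% power, 30% + 5% = 35% for the small difference, and 4% + 1% = 5% Type I error, as stated. A re-simulation of the design gave about 90% power with the stated allocation formula and 93% with equal allocation. The article does not give its simulation details, so this gap is not treated as an error, and nothing below depends on it. The stated power is presented for quit rates alone, with no covariates.

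**Chance of a trigger.** The article gives five factors; a 5% check on each, independently, is an assumption. Probability of at least one: 1 − 0.95^5 = 0.226, about 23%. With a 10% check: 1 − 0.90^5 = 0.410.

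**Power.** The documents give no predictor strengths, so these are assumed. Decisions use one final look at the .99 cut for either arm (|z| > 2.326, two-sided 0.02). The absolute power is below 95% because this is one fixed look at 625 patients, the average stopping size in a repeated-look design that can reach 1000. Only the differences matter here.

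*First simulation:* 4,000 trials, 625 patients at 1:1, 15.7% v 25.2%, five independent standard-normal covariates.

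| Log-odds per SD (odds ratio) | Unadjusted | Triggered | Always adjusted | Always minus triggered |
|---|---|---|---|---|
| 0.20 (1.22) | 73.0% | 73.0% | 74.7% | 1.7 |
| 0.35 (1.42) | 72.3% | 72.8% | 77.3% | 4.5 |

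*Second simulation:* 5,000 trials per setting, with the strength of the combined covariate score set by its AUC.

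| AUC | 238/387 patients, 15.7% v 25.2%: always v triggered | Gain | 500/500, 15.7% v 20.0%: always v triggered | Gain |
|---|---|---|---|---|
| about 0.58 | 69.60% v 68.68% | 0.92 | 30.88% v 30.00% | 0.88 |
| about 0.64 | 71.36% v 68.92% | 2.44 | 30.28% v 29.12% | 1.16 |
| about 0.70 | 73.62% v 69.24% | 4.38 | 30.74% v 28.28% | 2.46 |

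The two agree on a gain of about 1 to 5 points. With only the four predictors listed in Table 3, a rerun of the first setting gave 73.7% v 73.3% unadjusted and 76.7% v 73.4%, a gain over the unadjusted analysis of 0.4 to 3.3 points.

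**How often the decision changes.** In the first simulation, unadjusted and fully adjusted analyses disagreed at the .99 cut in 5.4% and 9.3% of trials (4.8% and 8.3% in a rerun). That is not the plan's rule. In the rerun, unadjusted and *triggered* analyses disagreed in 1.5% and 2.2% of trials at the expected rates, and in 0.3% and 0.2% under no difference.

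**Type I error.** With 500/500 patients, nominal 5%, one look and 12,000 trials per setting:

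| AUC | Unadjusted | Triggered, applied mechanically | Most favorable of three |
|---|---|---|---|
| about 0.58 | 5.42% | 5.30% | 6.07% |
| about 0.64 | 4.92% | 4.88% | 5.89% |
| about 0.70 | 4.76% | 4.65% | 6.15% |

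At the .99 cut, taking the better of the unadjusted and fully adjusted results raised the false-positive rate from about 2.0% to 2.4%.

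**The case against.** The strongest reply is that the plan does have a deciding analysis: a binomial model per arm, a prior, a stopping cut and a confirmation cut, echoed in Table 5 and Analyses by aim. This stands. A reader might infer that no single analysis decides the trial, or that stopping would rest on one model and confirmation on another. The article says neither. The fault is narrower: a later sentence allows departure from the stated default without saying what happens to the decision.

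Second, the sentence sits in a section about drift under changing allocation, and the baseline check in the Overview carries no adjustment rule of its own. This is fair, and the simulations of adjustment above have fixed allocation and no drift. But the sentence is not worded as limited to drift, and the ambiguity remains without any. The point about drift does bear on the remedy: simply deleting the sentence and adding baseline covariates would remove the section's only analytic response to change over time.

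Third, a reader might infer that planned power is lost. It is not: the stated 95% counts on no covariate gain, and the triggered rule performs about as well as the unadjusted analysis. What is forgone is an optional improvement.

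Fourth, a reader might infer that the investigators may pick the more favorable result. No section permits that; the 6% figure shows only what discretion could cost.

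Fifth, the imbalance criterion and the coding of covariates are details an article may leave to a fuller document. Agreed, and their absence is not the finding; the finding is the rule the article states. Likewise, income is not itemized in Table 3, but that table lists core measures and the eligibility section mentions demographics generally, so it cannot be concluded that income is uncollected.

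**Conclusion.** The concern holds in a limited form. The article states an unadjusted decision rule, then lets observed imbalance change the outcome analysis without saying whether the changed result governs the >.99 confirmation. The practical size is modest. Under an assumed 5% check on five independent factors, chance would invoke adjustment in about 23% of trials, and the triggered rule would alter the .99 decision in about 2% of trials at the expected rates. Always adjusting would gain about 1 to 5 points of power over triggered adjustment, or 0.4 to 3.3 points over the unadjusted analysis with the four predictors in Table 3. Mechanical use leaves Type I error essentially unchanged; unrestricted choice would take it to about 6% at a nominal 5%. All of these rest on assumed predictor strengths, an assumed trigger, a single look and no drift. The correction is worth making because the rule touches the primary decision and is easily repaired.

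**What to change.** Delete the imbalance trigger and name one deciding analysis in advance, by either route:

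- **Adjusted decider.** A Bayesian logistic model for 1-month verified abstinence with arm, cigarettes per day, time to first cigarette, age, sex and an enrollment-period term. It is used whatever the observed balance, at every look and for the >.99 confirmation. Re-simulate the operating characteristics under this model, and report the unadjusted result as a sensitivity analysis.
- **Unadjusted decider.** Keep the binomial model for both cuts, state that it alone decides, and always report the same fixed-covariate model as supportive only.

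Under either route, keep the drift monitoring as a secondary investigation that cannot change the deciding analysis.

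The second route costs a few sentences. The first also requires new simulations and imputation of the few missing covariates, for which Accounting for missing data already provides. Neither changes what patients experience or requires covariates beyond those in Table 3.

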#### Analyses by aim

The main analyses for each aim are outlined below (Table 5).

Aim 1. Hypothesis 1: among patients consented into the trial, significantly more patients in OPT OUT will participate in counseling, use cessation medications, and be abstinent from smoking at 1 month post randomization compared to OPT IN. These analyses will involve two-sample tests.

Aim 2. Hypothesis 2: significantly more smokers in OPT OUT will be abstinent from smoking, and mediation analyses will find that counseling participation, medication use, and default-theory-based variables will partially or fully explain the effect of OPT OUT on cessation at 6 months post randomization. After identifying a structural equation model that adequately fits the data for the hypothesized associations between the intervention and 6-month outcome, i.e., that Comparative Fit Index (CFI) > .9 and Root Mean Square Error of Approximation (RMSEA) < .8, we will examine mediation using approaches based on the work of MacKinnon et al. [49], Brown [50], and Shrout and Bolger [51]. Our theoretical model (Fig. 1, Significance) will guide our analysis.

Aim 2. Hypothesis 3: OPT OUT will be more costly—in terms of upfront costs—but will be more effective than OPT IN. As a result, OPT OUT will be more cost-effective from a provider perspective. We will conduct a cost-effectiveness analysis to explicitly document the relative costs and benefits of OPT OUT versus OPT IN. Our cost analytic framework generally follows the guidelines adopted by the Centers for Disease Control (CDC) in accordance with the Consensus Panel on Cost-effectiveness in Health and Medicine [52–54]. We will divide the analysis into two components: first, intervention-only costs, and second, intervention plus short-term (6 months or less) costs post discharge. The primary cost-effectiveness analysis will be set up as an incremental cost-effectiveness ratio (ICER). Incremental cost-effectiveness analysis identifies the marginal benefit of switching from one intervention to the other and is the ratio of the difference in costs divided by the difference in effectiveness between the two study arms. The outcome assessed will be biochemically or proxy-verified 7-day point-prevalence abstinence. The ICER will indicate the added cost per additional quitter OPT OUT versus OPT IN, a metric that will allow comparisons to other smoking-cessation economic studies. While the societal perspective is recommended by current national guidelines, it requires quality-adjusted life years (QALYs) as the denominator [52]. Since this is a short-term study, we decided against attempting to estimate changes in QALYs, and focus instead on cost per quit and incorporate costs from a health care system perspective (direct costs only), comparable to a-priori cost analyses of several clinical trials based in Kansas [55, 56]. In sensitivity analyses, we will adjust wage rates upwards to the national average. In order be able to generalize our findings from this one clinical trial to other populations, we will explore how the variation in counseling time and effectiveness influence the relative cost-effectiveness of the treatment strategies. Our analyses will vary time and effectiveness until breakeven points are achieved between the treatment options.

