#### Rationale for measuring main outcome at 1 month post intervention

The present study is focused on how best to engage smokers in tobacco-cessation treatment (i.e., counseling and medications) and quit. Assessing outcomes at 1 month will best capture the immediate impact of OPT IN versus OPT OUT on medication/counseling use, quit attempts, and abstinence [25, 26]. Moreover, assessing outcomes at 1 month is in accordance with Joint Commission Guidelines and UKanQuit standard practice for post-discharge follow-up of hospitalized smokers [27]. Perhaps most importantly, 1 month represents an important timeframe for hospitals, as hospitals with excessive 1-month readmission rates for selected diagnoses will receive decreased Medicare reimbursements [28]. Should our intervention prove effective, it could pave the way for future studies on the impact of smoking cessation on reduced 30-day readmission rates for specific diagnoses. Those who refuse consent at 1 month will not be eligible for inclusion again into the trial and they will be included (simply counted as smokers, because we will have no data on them) in our simplified intent-to-treat (ITT) analyses.

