### Project measures (Table 3)

#### Tobacco abstinence

Outcome measures are adapted from the Society for Research on Nicotine and Tobacco’s Workgroup on Abstinence Measures and Workgroup on Biochemical Verification [29, 30]. Our primary endpoint is 7-day, verified cigarette abstinence at 1 month after enrollment. Subjects with missing data will be counted as smokers.

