#### Plans for assuring data accuracy and protocol compliance

Data management activities for this project will encompass data entry, data cleaning, identifying and tagging any crossovers, conversion into proper format for data analysis and recoding. In addition, a computer-based tracking system will be developed to follow each patient and to prompt the staff for the upcoming data collection point. Data collection points for each subject will be calculated from their initial date of contact. Data entry will be performed on site under direction of the PI and the study statistician. Keypunching routines will adhere to the codebook specifications written by the team. Codebooks will include variable formats (numeric/alpha), min/max ranges and any skip patterns. Data will be double entered utilizing two separate databases and data entry personnel for the two databases would be different. Both the databases and the tracking system would be password protected for security and maintenance of confidentiality. At the end of each data entry period, data would be backed up onto a storage unit. Checks built into the database will ensure that individuals not meeting eligibility criteria are flagged and excluded from data analysis.

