#### Sensitivity analyses

To explore the effects of assuming MAR when data are actually MNAR (missing not at random) sensitivity analyses will be conducted using either a pattern mixture model or a selection model approach [42–45]. In addition, we will conduct and report an exploratory pooled ITT analysis to examine the effects of the Zelen design by calculating overall quit rates assuming patients who were dropped from the study due to failure to provide consent were (a) smokers, (b) nonsmokers, or (c) MNAR.

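### The main test of 1-month abstinence is defined on all randomized patients in some sections and on consenting patients only in another

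*Protocol article*

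**What the plan says.** Four sections of the protocol agree on one population for the main abstinence analysis.

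- Bayesian design: "The main outcome analysis will use an ITT approach, with the denominator being all participants randomized to the study".
- Rationale for measuring main outcome at 1 month, on those who refuse consent: "they will be included (simply counted as smokers, because we will have no data on them) in our simplified intent-to-treat (ITT) analyses".
- Tobacco abstinence: "Our primary endpoint is 7-day, verified cigarette abstinence at 1 month after enrollment. Subjects with missing data will be counted as smokers".
- Accounting for missing data: patients lost to follow-up are smokers in the main outcome analysis.

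Two later sections say something else.

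- Analyses by aim introduces its content as the main analyses and states Hypothesis 1, which includes 1-month abstinence, "among patients consented into the trial, significantly more patients in OPT OUT will participate in counseling, use cessation medications, and be abstinent from smoking".
- Sensitivity analyses refers to "patients who were dropped from the study due to failure to provide consent". It adds them back only in an exploratory pooled ITT analysis, under three assumptions: (a) smokers, (b) nonsmokers, (c) missing not at random.

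Table 5 restates Hypothesis 1 without naming a population. On timing, the delayed-consent rationale places consent after treatment. The month-1 section says "study staff will call all patients at 1 month post enrollment to assess outcomes including smoking status", with the invitation to take part coming at the end of that call.

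**The concern.** Scenario (a) of the exploratory analysis, refusers counted as smokers, is the analysis that the Bayesian design section and the 1-month rationale make the main one. The same analysis cannot be both main and exploratory. As written, either denominator could be defended from the protocol once results are known.

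The choice matters because of when consent is sought. By then the patient has had arm-specific contact, including up to four counseling calls by default in OPT OUT, and has just reported smoking status. Consent can therefore depend on both arm and outcome. Selecting on it gives up the randomized comparison and can create or hide a difference in quit rates. Patients who are never reached also never consent, so a consented-only set may lose more than the refusers.

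**Working it through.** **The plan's own figures.** Projected quit rates: OPT IN 0.30 × 0.29 + 0.70 × 0.10 = 0.157; OPT OUT 0.80 × 0.29 + 0.20 × 0.10 = 0.252. The planned effect is 9.5 points, as stated. A simulation of the described design (first look at 400 or 500, looks every 87 patients, thresholds 0.9925 and 0.99) gives a null success rate of 4.2 to 5.6%, against the stated 5%. Under the expected scenario it gives 89 to 93% power, against the stated 95%. The protocol does not give enough simulation detail to call the 95% wrong, and this point does not rest on it.

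**Refusal rates.** The protocol gives none for this trial and none by arm. The Discussion only remarks that most Zelen trials see single-digit percentages of refusal or crossover. All refusal rates below are assumptions.

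**Formulas.** Let q be the true quit rate, cq the probability that a quitter consents and cs the probability that a smoker consents.

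- Consented-only rate = q·cq / (q·cq + (1 − q)·cs)
- All-randomized rate, refusers as smokers = q·cq

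**No true difference between arms (OPT IN, then OPT OUT):**

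| q | Quitters refuse | Smokers refuse | Overall refusal | Consented-only rates | Spurious difference | All-randomized difference |
|---|---|---|---|---|---|---|
| 0.157 | 5%, 5% | 5%, 9% | 5%, 8% | 15.7%, 16.3% | +0.6 | 0 |
| 0.157 | 5%, 5% | 10%, 20% | 9%, 18% | 16.4%, 18.1% | +1.7 | 0 |
| 0.157 | 5%, 5% | 10%, 30% | 9%, 26% | 16.4%, 20.2% | +3.7 | 0 |
| 0.20 | 10%, 10% | 20%, 30% | 18%, 26% | 22.0%, 24.3% | +2.4 | 0 |
| 0.20 | 10%, 5% | 30%, 40% | 26%, 33% | 24.3%, 28.4% | +4.0 | +1.0 |

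Worked example, third row, OPT OUT: 0.157 × 0.95 = 0.149; 0.843 × 0.70 = 0.590; 0.149 / 0.739 = 20.2%.

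For scale, one standard error at 400 per arm is √(2 × 0.22 × 0.78 / 400) = 2.9 points.

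**Effect on the decision.** In the simulated design under the null, the second row gives a false OPT OUT win in about 8% of trials consented-only and under 3% all-randomized. The third row gives about 22% and about 2%. With equal 10% refusal unrelated to smoking, total type I error stays near 5% for either population.

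**The all-randomized rule is not neutral either.** Suppose refusal is unrelated to smoking but differs by arm.

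- 5% vs 9% under the null: 0.157 × 0.95 = 14.9% and 0.157 × 0.91 = 14.3%, a spurious −0.6 points; consented-only is unbiased here.
- 10% vs 30% under the null: 14.1% and 11.0%, a spurious −3.1 points.
- 10% vs 30% under the expected effect: 14.1% and 0.252 × 0.70 = 17.6%, and simulated power falls to about 26%.
- Equal 10% refusal only dilutes: 14.1% vs 22.7%, that is 8.6 points instead of 9.5.

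**The cap.** Bayesian design gives the maximum of 1000 both as patients consented and as patients enrolled, although enrollment is automatic at randomization. If 1000 means consented, 10% non-consent needs 1000 / 0.90, about 1112 randomized, and 20% needs 1000 / 0.80 = 1250.

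**The case against.** The strongest defence is that the primary rule is already fixed. Four sections agree on it, and the all-randomized denominator stands in the same paragraph as the interim analyses and adaptive updates. The conflicting phrase is one hypothesis sentence covering three outcomes, two of them secondary. Dropped could mean no further participation, and scenarios (b) and (c) are sensible bounds around the main rule. Much of this stands: all-randomized is the better-supported reading. It does not remove the conflict, because the hypothesis sentence sits under the main analyses and includes abstinence. Nor can consented be loose wording for enrolled, since the protocol separates automatic enrollment from consent at 1 month.

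It is also fair that single-digit refusal, the only guide in the document, makes the bias small.

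A reader might infer more than the text supports:

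- **That the posterior, allocation and stopping rule are left undefined.** They are not; their paragraph names the denominator.
- **That randomized patients are removed for ineligibility**, from "individuals not meeting eligibility criteria are flagged and excluded from data analysis". Eligibility is recorded before the randomize key is used and service records share the database, so this can mean filtering out screened patients who were never randomized.
- **That having no data on refusers contradicts the month-1 call.** The endpoint is verified abstinence by saliva or CO, and no data can mean no consented, verified endpoint.
- **That the outcome is known when consent is sought.** Only self-reported smoking status is recorded in the call before the request.

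**Conclusion.** The inconsistency is real, is in current text and concerns the primary endpoint. The all-randomized analysis with refusers and missing patients counted as smokers is clearly the better-supported version; Analyses by aim and Sensitivity analyses contradict it. Followed literally, the consented-only test would bias the comparison by about 0.6 points at single-digit refusal and by about 2 to 4 points at overall OPT OUT refusal of roughly 18 to 33%, against 9.5 points planned. These sizes rest on assumed refusal that differs by arm and by smoking status. The protocol neither gives nor rules out such rates, so a large bias is possible but not shown. The direction would reverse if the pattern of refusal did.

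**What to change.** 1. In Analyses by aim, name all randomized patients as the single primary population for 1-month abstinence, at the interims and at the end, with refusers and unreached patients counted as smokers.
2. In Sensitivity analyses, remove the wording that refusers were dropped and acknowledge that scenario (a) is the main analysis. Keep (b) and (c) as sensitivity analyses, and add the consented-only comparison as a labelled sensitivity analysis.
3. State whether 1000 counts randomized or consented patients.
4. Report non-consent and non-contact by arm, since the main rule dilutes the effect and can bias it if refusal differs by arm.
5. Counseling and medication outcomes may stay on patients with usable data if labelled secondary with that population stated. Medication days are self-reported, and the protocol does not say whether refusers' counseling records may be used.

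The cost is protocol wording plus one table of non-consent and non-contact by arm. Quit rates on all randomized patients will be lower than among consenters.
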